### MRI acquisition and functional tasks

2.5

MRI acquisitions will be conducted on a Siemens Magnetom Prisma Fit 3 T device at Hospital Clínic of Barcelona and will last approximately 45 min. We will instruct participants to remain still and place pads around their heads to minimize head movement.

The MRI acquisition protocol will include a high-resolution T1-weighted structural Three-dimensional Magnetization-Prepared Rapid Acquisition with Gradient Echo (3D-MPRAGE) sequence (repetition time (TR) 2,300 ms; echo time (TE) 3 ms; inversion time (TI) 900 ms; flip angle 9°; 240 sagittal slices with 1 mm×0.94 mm×0.94 mm voxel size and 256 × 256 matrix size), a multi-shell DWI sequence (90 diffusion encoding directions and two different phase encoding directions (AP and PA); b-values 1,000, 2000, and 3,000 s/mm^2^; five b0 volumes; TR 5400 ms; TE 113 ms; 100 transverse slices with 1.5 mm isotropic voxel size and 150 × 150 matrix size), a single voxel spectroscopy (SVS) localized in the left dorsomedial prefrontal cortex (with and without water suppression, with 96 and 16 acquired averages, respectively; TR 3000 ms; TE 30 ms; 20x30x15mm voxel size), two gradient-echo echo-planar (EPI) sequences for the cognitive tasks (TR 1500 ms; TE 37 ms; 72 transverse slices with 2 mm isotropic voxel size and 104 × 104 matrix size), and their corresponding gradient field mapping (GFM) to estimate and correct susceptibility artifacts caused by lack of homogeneity in the field. We will inspect the images visually to detect anomalies or artifacts.

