#### N-Back paradigm

2.5.1

The sequential-letter version of the n-back working memory task (duration: 8 min 42 s) evaluates two levels of working memory load (1-back and 2-back) in a block-design manner. During the blocks, a projector displays a single letter on the screen every 2 s (1 s on, 1 s off). Each block consists of 24 letters, including five randomly located targets. In the 1-back blocks, the letters are color-coded in green. Participants must detect those that are the same as the one presented just before (e.g., the letter “J” in the sequence “A-K-J-J”). In the 2-back blocks, the letters are color-coded in red. Participants must detect letters that are the same as the one presented before the last (e.g., the letter “K” in the sequence “G-K-O-K”). Participants must indicate targets by pressing a button. Four 1-back and four 2-back blocks are presented interleaved. Between them, the baseline stimulus (an asterisk flashing with the same frequency as the letters) is shown for 16 s. Participants will undergo a training session outside of the scanner before starting.

To measure participants’ performance in the n-back, we will use the signal detection theory index of sensitivity, d′ (47), which separately analyses true and false positives. We will exclude participants with negative d′ values in either or both 1-back and 2-back versions of the task, as negative values suggest that participants are not performing the task effectively.

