Finally, we will preprocess fMRI data using fMRIPrep (62), which includes motion correction, slice time correction, susceptibility distortion correction using the GFM, 4 mm FWHM Gaussian smoothing, detrending, and high-pass temporal filter with a 128 s cut-off. Following preprocessing, we will conduct the first-level (individual) analysis to obtain activation maps by fitting a GLM to the preprocessed images using the Nilearn toolbox. We will design the model’s regressors to capture changes in the BOLD signal corresponding to each stimulus, convolving task-related temporal representations with the canonical Glover hemodynamic response function. Nuisance regressors derived from fMRIPrep will be incorporated into the design matrix to minimize the residual error. For n-back, we will compute the following contrasts: 1-back vs. baseline, 2-back vs. baseline, and 2-back vs. 1-back. We will compute the following contrasts for verbal memory: recall vs. control, encoding vs. control, and recall + encoding vs. control. Finally, utilizing the anatomical scan, the activation maps will be spatially normalized to a 2 × 2 × 2 mm^3^ MNI template by employing the ANTs registration toolbox in preparation for subsequent second-level analysis.

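### The 128 s high-pass cut-off equals the n-back task's own 128 s cycle, so the filter removes part of the load-specific signal, including in the primary 2-back contrast

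*Protocol article*

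**What the plan says.** The protocol article fixes the task timing and the filter in separate places.

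- **Task (section 2.5.1).** One letter appears every 2 s. "Each block consists of 24 letters, including five randomly located targets". "Four 1-back and four 2-back blocks are presented interleaved", and between blocks "the baseline stimulus (an asterisk flashing with the same frequency as the letters) is shown for 16 s". The stated total duration is 8 min 42 s.
- **Acquisition (section 2.5).** The task sequences have a TR of 1500 ms.
- **Filter and model (section 2.6).** Preprocessing includes detrending and a "high-pass temporal filter with a 128 s cut-off". A first-level GLM with the Glover response function is then fitted to the preprocessed images, with nuisance regressors from fMRIPrep that are not listed. The n-back contrasts are each load against baseline, and 2-back against 1-back.
- **Primary outcome (section 2.7).** The pre-post change in 2-back versus baseline activation, in three prefrontal regions, is correlated with the change in FAST.

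The article does not state the task's cycle length or relate the cut-off to it.

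**The concern.** A high-pass filter should remove scanner and physiological drift that is slower than the task. Its cut-off is therefore normally set well above the longest period at which a condition repeats. Here the two coincide. The filter cannot tell drift from the alternation between 1-back and 2-back, so part of that alternation is removed along with the drift.

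The part at risk is the load-specific response, on which 2-back versus 1-back depends almost wholly and 2-back versus baseline depends in part. The primary measure is a difference between two scans, so noise from both scans enters it. Section 2.2 plans for 28 participants and about 80% power at r = 0.56, which leaves little room for avoidable measurement error.

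**Working it through.** **1. Cycle length.** Block: 24 letters x 2 s = 48 s. Block plus baseline: 48 + 16 = 64 s. With the loads alternating, one load recurs every 2 x 64 = 128 s, exactly the cut-off.

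**2. Check against the stated duration.** 8 min 42 s = 522 s. Eight blocks with eight baselines take 8 x 64 = 512 s, 10 s short of 522 s, which fits a short lead-in or lead-out. Eight blocks with seven baselines take 384 + 112 = 496 s, so the first block can start at most 522 - 496 = 26 s into the run. Nine baselines would give 384 + 144 = 528 s, which is too long. The stated duration supports the timings and bounds the lead-in at 0-26 s.

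**3. What the filter removes.** The run has 522 / 1.5 = 348 volumes. A cosine drift basis at 128 s has floor(2 x 522 / 128) = 8 terms, and the fastest has period 2 x 522 / 8 = 130.5 s, next to the task's 128 s. At 256 s there are floor(2 x 522 / 256) = 4 terms, the fastest with period 261 s.

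Blocks were convolved with a Glover response. At 128 s the drift space contains 32-63% of the variance of the 2-back regressor and 42-71% of that of the 2-back minus 1-back difference. It contains only 1-7% for the sum of the two loads, which cycles at 64 s.

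**4. Cost in precision, with the filter in both data and model.** The table gives contrast variance with the 128 s filter divided by variance with no filter, under white noise.

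| First block starts at | 2-back vs baseline, 1-back first | 2-back vs baseline, 2-back first | 2-back vs 1-back |
|---|---|---|---|
| 0 s | 1.18 | 1.45 | 2.19 |
| 5 s | 1.15 | 1.26 | 1.81 |
| 10 s | 1.18 | 1.17 | 1.72 |
| 16 s | 1.36 | 1.15 | 1.99 |
| 26 s | 1.95 | 1.43 | 3.56 |

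Information kept is the reciprocal:

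- 2-back versus baseline: 1/1.95 to 1/1.15, or 51-87%. With a lead-in of 10 s or less it is 69-87%.
- 2-back versus 1-back: 1/3.56 to 1/1.72, or 28-58%.
- With a 256 s cut-off: 93-100% and about 94-96%.

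**5. Does a longer cut-off let in too much drift?** With 20-60% of the noise variance taken as 1/f drift (an assumption), moving from 128 s to 256 s still lowers first-level variance by about 12-40% for 2-back versus baseline and 24-64% for 2-back versus 1-back.

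**6. If only the data were filtered.** A true 2-back effect of 1.0 would be estimated at:

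- 0.89-1.01 if 1-back activates equally;
- 0.70-0.91 if 1-back activates half as much;
- 0.52-0.82 if 1-back does not activate.

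**7. Illustration for the correlation.** Let first-level noise be a share s of the variance of the change score at a 256 s cut-off, and let g be the variance reduction from step 5. The correlation under the 128 s filter is then r / sqrt(1 + s x (1/(1 - g) - 1)). Take r = 0.56:

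- s = 10%, g = 12%: 0.56 / sqrt(1.014) = 0.56.
- s = 30%, g = 40%: 0.56 / sqrt(1.200) = 0.51.

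The shares are assumptions; the article gives none.

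**The case against.** Much of the case on the other side stands.

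- **The primary contrast is the less affected one.** The heaviest loss falls on 2-back versus 1-back, which is secondary. For 2-back versus baseline, activation shared with 1-back passes almost untouched. The worst figures need a late first block, and the lead-in is not stated.
- **Bias is not shown.** Because filtering is listed under preprocessing and the GLM is fitted afterwards, a reader might infer that the design is left unfiltered and the estimates are biased. The article does not say so. It adds nuisance regressors without listing them, so drift terms in the model are neither stated nor excluded, and a condensed article may leave that to the full plan. The figures in step 6 are conditional.
- **The effect on the study's test is not established.** A reader might infer that the filter seriously undermines the primary correlation or its power. First-level noise is only one part of the variance of a regional pre-post change; true differences between patients and session effects are others, and the article gives no split.
- **No fault can be shown for the verbal memory task.** The same filter applies to it, but section 2.5.2 gives no phase durations, so its cycle cannot be computed.
- **256 s is not uniquely right.** The best cut-off depends on the drift spectrum of this scanner and these patients. The direction of the gain held under every noise model tried.

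None of this removes the coincidence in steps 1 and 2 or the loss of precision, which appeared for every lead-in and order tried. Strict alternation is not essential either: two other interleaved orders lost 45-49% of the variance of the 2-back regressor.

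**Conclusion.** The point holds as one of precision. The stated cut-off equals the cycle implied by the article's own timings, and part of the load-specific signal is lost as a result: about 51-87% of the information remains on the primary contrast and 28-58% on 2-back versus 1-back. These ranges assume alternating blocks, a cosine drift basis, a lead-in of 0-26 s and white noise.

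If data and design are filtered identically, the estimates stay unbiased. If only the data are filtered, the 2-back estimate is also pulled towards zero unless both loads activate about equally. The correlation with FAST change would move towards attenuation; the size cannot be derived from the article and is probably modest. The timing equality is certain and the downstream effect is not. This should be corrected before analysis, but it does not invalidate the design.

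**What to change.** For the n-back first-level model, set the high-pass cut-off clearly above the 128 s task cycle, for example 256 s (twice the cycle). Enter the drift terms as cosine regressors in the same GLM instead of filtering the data beforehand, so that data and design are treated identically at both scans. State the cycle length next to the cut-off so that the choice can be checked.

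The cost is one analysis parameter and a sentence of text, with no new data. The downside is that slightly more slow drift stays in the residuals; even so, first-level variance fell under all the white and white plus 1/f noise models tried.

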### Sample size estimation

2.2

We aim to include 28 participants because previous studies with 23–28 participants found effects (29–31). In addition, with this sample size, we would have ~80% power to detect moderate correlations (r 0.56) after correcting for multiple testing (correlations in three ROIs: left dorsolateral, bilateral dorsomedial, and right dorsolateral prefrontal cortices). Note that this sample size does not include those patients who, even if consenting to participate, leave the study before finishing the baseline assessment and MRI acquisition.

As we anticipate the possibility of participant attrition during the follow-up, we plan to enroll 32 participants (i.e., ~15% more) to counteract the potential dropouts.

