### Data analysis

2.7

The primary outcome will be the correlation between pre-post changes in the activation of the dorsolateral and dorsomedial prefrontal cortex during the working memory n-back task (2-back vs. baseline) and pre-post changes in psychosocial functioning assessed with the Functioning Assessment Short Test (FAST) (63). Specifically, we will conduct three correlations: one for the left dorsolateral, one for the bilateral dorsomedial, and one for the right dorsolateral prefrontal cortex. We will use a permutation test to correct for multiple testing (three correlation tests).

For the secondary analyses, we will conduct two kinds of correlations: (a) pre-post changes in MRI data with pre-post changes in cognition and psychosocial functioning outcomes, and (b) baseline MRI data with pre-post changes in cognition and psychosocial functioning outcomes. We will include as covariates the variables from age, sex, bipolar disorder type, medication (use of lithium, antiepileptics, antidepressants, and antipsychotics), illness history (duration of the illness and number of episodes), or educational level that show statistically significant associations with the MRI signal or the cognition/functioning outcome; in case that several variables show statistically significant associations, we will select those still showing statistical significance in multiple regression. We will report results for structural MRI analyses using both familywise error rate (FWER) < 0.05 based on conservative permutation tests (64) and threshold-free cluster enhancement (TFCE) (65) and uncorrected *p* < 0.001 (at the exploratory level). For spectroscopy, we will use linear models. Finally, for fMRI analyses, a paired t-test will be conducted on single-subject contrast to examine temporal changes in activation, employing the Nilearn toolbox. We will break down and localize clusters using SDM ‘imgcalc’ tool (66).

We will also repeat all the analyses on those results that reach statistical significance according to sex to explore potential differences.

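### No group-level analysis checks or adjusts for pre-post change in head motion, although the primary result is a correlation between two change scores

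*Protocol article*

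**What the plan says.** Motion is addressed at several stages of the protocol article.

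- **Acquisition (section 2.5).** "We will instruct participants to remain still and place pads around their heads to minimize head movement". Quality control of the images is visual: "We will inspect the images visually to detect anomalies or artifacts".
- **Diffusion data (section 2.6).** The pipeline includes eddy-current and motion correction.
- **fMRI (section 2.6).** fMRIPrep performs motion correction, and at the first level "Nuisance regressors derived from fMRIPrep will be incorporated into the design matrix to minimize the residual error". The text does not say which regressors these are.
- **T1 data (section 2.6).** The volume, thickness and surface-area pipelines name no motion step, so visual inspection is the only image-level safeguard described.

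At group level (section 2.7), the primary analysis is stated as follows: "Specifically, we will conduct three correlations", one per prefrontal region, each relating activation change (2-back versus baseline) to FAST change. Multiplicity is handled by permutation: "We will use a permutation test to correct for multiple testing (three correlation tests". No covariate is given for these tests. For the secondary analyses, the candidate covariates are age, sex, bipolar type, medication, illness history and education. The Discussion's list of further confounders does not name motion either.

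**The concern.** Realignment and first-level regressors act inside one run. They do not by themselves remove the effect of a participant moving more at one session than at the other, and the primary inference rests on that between-session difference. Participants are aged 60 or over and may be only partly remitted. It is conceivable, though the documents neither state nor test it, that those who improve also lie stiller at the second scan. Motion change would then be a common cause of both change scores.

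The study has no control arm and rests on within-group correlation of changes, so a third variable that moves with both is a leading threat to interpretation. Permuting to correct for three tests does not protect against it. Structural and diffusion change face the same question, and T1 measures have the least stated protection. At stake is whether a positive correlation can be read as a neural correlate of functional improvement.

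**Working it through.** **Inputs from the protocol article.** Section 2.2 gives an analysed sample of 28, three regions and a target correlation of 0.56: "we would have ~80% power to detect moderate correlations (r 0.56) after correcting for multiple testing". The significance level and sidedness are not stated; 0.05 two-sided is assumed, which is 0.05/3 = 0.0167 per region by Bonferroni.

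**Inputs that are assumptions.** Let a be the correlation of motion change with activation change in each region, and b that of motion change with FAST change. Neither is in the documents, so a = b is varied from 0.2 to 0.5. The correlation between regions is set at 0.5.

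**Step 1: reproduce the stated power.** By Fisher's z, power = Φ(atanh(r)·√(n − 3) − z), with z = 2.394 for 0.0167 two-sided.

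atanh(0.56) = 0.633 and √25 = 5, so power = Φ(3.164 − 2.394) = Φ(0.770) = 77.9%.

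Simulating the t-test of the Pearson correlation gives 79.2%. The stated figure of about 80% is reproduced.

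**Step 2: size of the spurious correlation.** With no direct link between activation change and FAST change, their correlation through motion is a·b.

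**Step 3: false positives in any of the three regions.** Simulated with n = 28 and no true link, in two settings:

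- Setting A uses the maximum absolute correlation over the three regions (critical value 0.442, close to what the permutation test would use), with a total inter-region correlation of 0.5.
- Setting B uses Bonferroni, with 0.5 as the inter-region correlation left after motion.

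| a = b | Spurious r = a·b | Setting A | Setting B |
|---|---|---|---|
| 0.2 | 0.04 | 5.6% | 4.9% |
| 0.3 | 0.09 | 7.8% | 6.9% |
| 0.4 | 0.16 | 14.5% | 12.9% |
| 0.5 | 0.25 | 30.0% | 26.1% |

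For motion alone to produce the planned 0.56, a and b would each have to be about 0.75 (0.75² = 0.5625).

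**Step 4: effect of adjustment.** The partial correlation given motion change m is (r_xy − r_xm·r_ym) / √((1 − r_xm²)(1 − r_ym²)). With it, the family-wise error stays near nominal for every a and b tried: about 5% in setting A and 4.3 to 4.5% in setting B.

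**Step 5: cost in power.** One covariate replaces n − 3 by n − 4: Φ(0.633·√24 − 2.394) = Φ(3.100 − 2.394) = Φ(0.706) = 76.0%. This assumes that the partial correlation is still 0.56.

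**The case against.** A reader might infer that motion is handled only by regressors and visual inspection. The article does not support that. Pads and instructions, fMRIPrep realignment and diffusion motion correction are all planned, and the description comes close to true only for T1 data, which serve secondary, exploratory aims.

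A reader might also infer that a positive primary result would probably be an artefact. That is not supported either:

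- The size of the bias rests wholly on assumed links, and at 0.2 there is essentially no inflation.
- The contrast compares interleaved blocks within one run. Motion unrelated to block timing would mainly add noise and weaken a correlation; a directional bias needs motion that follows the blocks or otherwise shifts the contrast consistently.
- No passage shows that improvers move less.

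A third argument is that a condensed article may leave motion detail to a fuller document. For a numeric run-exclusion limit this stands, and its absence is not held against the plan. It is weaker for the group-level model, because the article writes out the adjustment set and motion is not in it. That list does sit in the paragraph on secondary analyses and so does not govern the primary tests, but for those no covariate is stated at all.

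Finally, adjustment is not free of risk. If task engagement affects both movement and activation, conditioning on motion can remove real signal. This argues for a sensitivity analysis rather than a replacement primary estimate.

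**Conclusion.** The concern holds in a limited form. Motion is reduced at acquisition and corrected within the fMRI and diffusion acquisitions, but no stated group-level analysis checks or adjusts for its pre-post change. The consequence is conditional. If motion change correlates at about 0.2 or less with both sides, it is negligible. At about 0.4 with both, the family-wise error is 13 to 14.5%, and at 0.5 it is 26 to 30%. These figures assume n = 28, a 0.05 two-sided family-wise level, an inter-region correlation of 0.5 and no true effect. The documents cannot say where in this range the study lies, but its own scans can show it. It is a worthwhile, low-cost improvement to what a positive result can support, not a flaw that invalidates the primary analysis.

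**What to change.** 1. Keep the three primary correlations as planned.
2. Pre-specify a sensitivity analysis in section 2.7. Report each of the three as a partial correlation given change in mean framewise displacement of the n-back run, as computed by fMRIPrep, beside the unadjusted value. Report the correlation of motion change with FAST change as well.
3. State in advance that a primary result that disappears on adjustment will not be read as a neural correlate of improvement.
4. Add a session-level motion or image-quality term to the candidate covariates for the structural and diffusion change models.

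The cost is wording and a small amount of analysis; no new scans or assessments are needed. The adjusted estimate loses one degree of freedom, taking power at 0.56 from about 78% to 76%. Because adjustment may also remove some genuine signal, both estimates should be reported.

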### Data analysis

2.7

The primary outcome will be the correlation between pre-post changes in the activation of the dorsolateral and dorsomedial prefrontal cortex during the working memory n-back task (2-back vs. baseline) and pre-post changes in psychosocial functioning assessed with the Functioning Assessment Short Test (FAST) (63). Specifically, we will conduct three correlations: one for the left dorsolateral, one for the bilateral dorsomedial, and one for the right dorsolateral prefrontal cortex. We will use a permutation test to correct for multiple testing (three correlation tests).

For the secondary analyses, we will conduct two kinds of correlations: (a) pre-post changes in MRI data with pre-post changes in cognition and psychosocial functioning outcomes, and (b) baseline MRI data with pre-post changes in cognition and psychosocial functioning outcomes. We will include as covariates the variables from age, sex, bipolar disorder type, medication (use of lithium, antiepileptics, antidepressants, and antipsychotics), illness history (duration of the illness and number of episodes), or educational level that show statistically significant associations with the MRI signal or the cognition/functioning outcome; in case that several variables show statistically significant associations, we will select those still showing statistical significance in multiple regression. We will report results for structural MRI analyses using both familywise error rate (FWER) < 0.05 based on conservative permutation tests (64) and threshold-free cluster enhancement (TFCE) (65) and uncorrected *p* < 0.001 (at the exploratory level). For spectroscopy, we will use linear models. Finally, for fMRI analyses, a paired t-test will be conducted on single-subject contrast to examine temporal changes in activation, employing the Nilearn toolbox. We will break down and localize clusters using SDM ‘imgcalc’ tool (66).

We will also repeat all the analyses on those results that reach statistical significance according to sex to explore potential differences.

